### Smartphone-based intervention

In all conditions, the training will consist of five distinct phases in total (see Fig. 2): As an initial step, a preparatory phase will serve as a baseline and resting period for physiological measures. Then, a mood induction phase will be initiated to induce a depressed mood prior to the first training phase. After the first training phase, a second mood induction and a second training phase will follow. Preparatory phase and both mood induction phases will be identical for all participants. The two training phases will differ depending on the condition that each participant has been allocated to.

During the preparatory phase, different stimuli will be presented to the participant via smartphone. These will alternate between live self-recordings of the participant and verbal stimuli: “hopeless” and “happy” as words congruent or incongruent with depressiveness, respectively, and “me,” “the world,” and “the future” corresponding with Beck’s cognitive triad of depression [42]. Each stimulus will be presented for five seconds in randomized order following the display of a fixation cross (3 s.) and will be shown twice, adding up to a total of twelve stimulus presentations. Before the first and after each stimulus presentation, two one-item self-reports of the current level of depressed and positive mood, respectively, will be collected.

The subsequent mood induction will follow a validated procedure [43, 44] and consist of ten depressogenic cognitions shown on-screen (e.g., “*My future is absolutely hopeless*”), which the participant will read aloud while listening to music inducing depressed mood (i.e., excerpt from “Adagio in G minor” by Tomaso Giovanni Albinoni). After the mood induction, participants will again rate their current level of depressed and positive mood.

#### Training for the three intervention conditions

The two training phases will each start with detailed instructions by both the study therapist *and* on-screen via text and animations. In two subsequent practice runs, participants will then familiarize themselves with the respective exercises. Following these practice runs, each training phase will consist of 20 trials, appearing in a randomized order, accompanied by mood ratings. In all intervention conditions, participants will receive instructions and feedback with reinforcing statements, pictures, and animations in the smartphone app. Further, the study therapist will provide support and feedback throughout the training and, in the CR and CR + AFE conditions, rate the performance of the participants via the app. The app will be controlled by the study therapist with a computer tablet that will be connected to the app via a secure local network.

During the training, participants will be confronted with negative, depressogenic (e.g., ‘*I am a complete failure’)* and anti-depressive cognitions (e.g., ‘*I can do this’)* on the smartphone screen. Participants are instructed to read the statements aloud, briefly rate their mood, and counteract the depressogenic/strengthen the anti-depressive cognitions in different fashions, depending on the study condition (see Fig. 3). The sequence of the training phases will be balanced, so that half of the participants start with the depressogenic, and half with the anti-depressive cognitions. The cognitions used in the training will consist of items from the Beck Hopelessness Scale (German version: [45]), the Cognitive Triad Inventory (German version: [46]), the Automatic Thoughts Questionnaire (German version: [47]), and the Rosenberg Self Esteem Scale (German version: [48]) adapted and complemented by a team of three clinical psychologists with expertise in cognitive behavioral therapy for depression (including the senior author). Depending on the study condition, participants are instructed to deal with the statements in different fashions:

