In the present study, we aim to fill these gaps in the depression and CBT literature pertaining the role of kinesthetic input (facial expression) in the modification of depressive mood. The study, “EmpkinS-EKSpression” is part of the Collaborative Research Center (CRC) “Empatho-Kinaesthetic Sensor Technology – Sensor Techniques and Data Analysis Methods for Empatho-Kinaesthetic Modeling and Condition monitoring” (EmpkinS, CRC 1483, German Research Foundation). Its overarching goal is to derive information about clinically relevant states from minimally disturbing and non-invasive assessments of motion for research, diagnostic, and intervention purposes. Specifically, we intend to examine the extent to which the efficacy of an automated, smartphone-based cognitive reappraisal training (as a key cognitive restructuring technique) against depressed mood can be augmented by systematically pairing the vocalization of depressogenic self-statements with invalidating kinesthesia and the vocalization of anti-depressive self-statements with validating kinesthesia, respectively. We further aim to clarify the extent to which singular markers as well as the combined pattern of kinesthetic indicators are associated with depression and could, hence, be employed for the automated detection of depression.

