#### Training for the sham control condition

For the sham control condition, the training consists of allocating geometric forms to a target object based on either their color (Training Phase 1) or their shape (Training Phase 2) in order to control for effects of interacting with a study therapist and a smartphone, as well as activation related to study participation.

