#### Efficacy of the reappraisal training augmented with facial expressions

In order to study the effectiveness of the EmpkinS-EKSpression app-based interventions, generalized linear models (GLMs) of the between-subject factors “diagnostic group” (with depression vs. without depression) and “intervention condition” (CR vs. CR + AFE vs. AFE vs. sham control), as well as the within-subject factor “time of assessment” will be applied in a stepwise fashion.

Regarding the primary outcome of depressed mood, we will first examine whether the mood induction phase *induces* depressed mood using a paired *t*-test with the pre- and post-mood-ratings as dependent variable (manipulation check). Further, hierarchical linear models (HLMs) will be implemented to assess whether the EmpkinS-EKSpression app-based interventions are effective in *reducing* depressed mood. As a first step, we will compare the CR condition with the sham control condition and the CR + AFE with the CR condition to study whether cognitive reappraisal training can be augmented with anti-depressive kinesthesia. As a second step, we will compare the AFE condition with the sham control condition. For continuously assessed secondary outcomes (i.e., positive mood, app data), corresponding analyses will be conducted.

With regard to secondary outcomes (i.e., GRID-HAMD, CES-D, current suicidality, ERSQ-ES, DAS-A, ATQ-R) assessed at pre-treatment, post-treatment, and/or follow-up, as well as pre/post mood-ratings, we will implement mixed analyses of variance (ANOVAs), again with the between-subject-factor, “study condition” (CR, CR + AFE, AFE, sham control) and the within-subject factor, “time.” Feasibility measures (treatment integrity, compliance, usability, acceptability) will be descriptively analyzed and contrasted between study conditions utilizing one-way ANOVAs. Finally, changes in kinesthesia and other psychophysiological measures over the course of the intervention, as well as differences between diagnostic groups and intervention conditions will be examined using, again, HLMs. All analyses will be conducted using the whole sample, as well as with the added between-subject-factor, “diagnostic group” (with vs. without depression). All analyses will be conducted with a significance level of α = 0.05. One-tailed tests will be used when the algebraic sign of the test statistic is specified; otherwise, two-tailed tests will be used.

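### The factors named for the mood analysis leave out stimulus type, phase and order, although the training session is built on them

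*Protocol article*

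**What the plan says.** All places are in the Protocol article.

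- **Session structure** (Smartphone-based intervention): "After the first training phase, a second mood induction and a second training phase will follow". The first training phase also follows a depressed-mood induction, and "Preparatory phase and both mood induction phases will be identical for all participants".
- **Active arms** (Training for the three intervention conditions): "each training phase will consist of 20 trials, appearing in a randomized order, accompanied by mood ratings". One phase uses depressogenic and the other anti-depressive statements, and participants "counteract the depressogenic/strengthen the anti-depressive cognitions in different fashions, depending on the study condition". On order: "The sequence of the training phases will be balanced, so that half of the participants start with the depressogenic" statements.
- **Ratings** (Primary outcome): depressed mood is rated twice per trial, once after the opening statement is read and once after the last step.
- **Sham** (Training for the sham control condition): geometric forms are sorted "based on either their color (Training Phase 1) or their shape (Training Phase 2"). No depressogenic or anti-depressive statements are described.
- **Aim** (Background, last paragraph): reappraisal is to be augmented by "systematically pairing the vocalization of depressogenic self-statements with invalidating kinesthesia and the vocalization of anti-depressive self-statements with validating kinesthesia, respectively".
- **Analysis** (Efficacy of the reappraisal training augmented with facial expressions): the named factors are diagnostic group and intervention condition, "as well as the within-subject factor “time of assessment” will be applied in a stepwise fashion". Depressed mood is then analysed by hierarchical linear models (HLMs), comparing CR with sham, CR + AFE with CR, and AFE with sham. Pre/post mood ratings go into a mixed ANOVA of condition and time.

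**The concern.** Stimulus type, phase and order are deliberate parts of the design, and none is among the named factors. This has two consequences for a model with one time factor. At any trial position, one part of an active arm has just read depressogenic statements and the other part anti-depressive ones, so the time-specific mean mixes the two and their difference goes into the residual. The series also contains a second induction intended to worsen mood, so a single time course describes two separate recoveries as one.

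At stake are the precision of time-based contrasts, protection if order is unevenly split within an arm, and the ability to see an augmentation effect that is present with one kind of statement and absent with the other.

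**Working it through.** **1. The plan's own figure.** Inputs (Participants): d = 0.5, two-sided α = 0.05, power 0.80. The normal formula gives n = 2(1.960 + 0.842)²/0.5² = 62.8, so 63 per arm. The exact t-test gives 63.77, so 64, and 4 × 64 = 256, which matches. The 64 per condition pools both diagnostic groups (2 × 32). By the normal approximation, power at 64 is Φ(0.5/√(2/64) − 1.960) = Φ(2.828 − 1.960) = 0.81.

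**2. What one time point contains.** Training yields 2 phases × 20 trials × 2 ratings = 80 ratings. Of these, 40 come straight after reading: 20 after depressogenic and 20 after anti-depressive statements.

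| | Order A | Order B |
|---|---|---|
| Phase 1, after induction 1 | depressogenic | anti-depressive |
| Phase 2, after induction 2 | anti-depressive | depressogenic |

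Within a row the two order groups differ in stimulus. Over the whole session each person has 20 trials of each type.

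**3. Precision.** The documents give no SD or order effect, so a range is assumed. Take SD 1 within an order group and a difference of o SD between order groups. A 50:50 mix adds o²/4 to the variance. Power for two active arms of 64 is Φ(2.828/√(1 + o²/4) − 1.960).

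| o (SD) | √(1 + o²/4) | Power |
|---|---|---|
| 0 | 1.000 | 0.81 |
| 0.25 | 1.008 | 0.80 |
| 0.5 | 1.031 | 0.78 |
| 1 | 1.118 | 0.72 |

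This treats order as varying at random between participants. With exactly 32:32 in each arm, only the estimated standard error is inflated. Power is then Φ(2.828 − 1.960 × √(1 + o²/4)) = 0.80, 0.79 or 0.74 for the three non-zero effects. Against sham, only one arm carries the extra variance, so the loss is smaller.

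**4. Bias.** A simulation (4,000 runs, 64 per arm, within-person correlation 0.7) used a true contrast of 0.50, a stimulus effect of 1 SD, and a 0.5 SD carry-over into phase 2 for those starting with depressogenic statements. With 50:50 order in both arms, the session-average contrast was 0.50 with or without an order term. With 60:40 or 70:30 in one arm, the unadjusted estimate was 0.48 or 0.45 and the order-adjusted estimate 0.50. Arithmetic agrees: 38 of 64 gives 0.50 − (0.594 − 0.5) × 0.5/2 = 0.48, and 45 of 64 gives 0.50 − (0.703 − 0.5) × 0.5/2 = 0.45.

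**5. Dilution.** Suppose a 0.5 SD effect exists with one statement type only. The session average then shows 0.25. With within-person correlation r between phases, the average has SD √((1 + r)/2). Power is Φ(0.25/(√((1 + r)/2) × √(2/64)) − 1.960) = 0.37 at r = 0.5 and 0.31 at r = 0.9. That statement type analysed alone has 0.81.

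**6. Are the added terms informative?** Condition-by-stimulus-type between two active arms uses within-person differences with SD √(2(1 − r)). For a difference of 0.5 SD, power is 0.67, 0.81 or 0.95 at r = 0.3, 0.5 or 0.7. Condition-by-order, with 32 per arm and order, has standard error √(4/32) = 0.354 and power Φ(0.5/0.354 − 1.960) = 0.29, so it is not a useful test.

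**The case against.** The strongest reply is that the randomised comparison is sound as it stands, and much of this reply holds.

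- A reader might infer that the two phases pull mood in opposite directions. The text does not support that. Depressogenic statements are to be counteracted and anti-depressive ones strengthened, and in CR and CR + AFE the trials of both phases close with rereading of affirming and self-supporting statements. Only the rating straight after the opening statement follows opposite content.
- A reader might infer that carry-over biases the condition effect. Each participant stays in one condition throughout, so mood carried into phase 2 is part of that condition's effect. With order balanced within arms, step 4 shows no bias.
- A reader might assume an SD of 2.5 and stimulus differences of 1, 2 or 3 points, and conclude that 64 per arm act like about 62, 55 or 47 (64 × 6.25/(6.25 + D²/4)). That could describe a single time-specific rating. It does not describe the session average, where stimulus type is balanced within each person.
- The Background and Discussion ask whether reappraisal as a whole is augmented. An effect per statement type is not the stated question.
- The HLM sentence lists no fixed effects, and the article is condensed. It cannot be read as saying that no analysis will ever include these factors. Nor does it define which ratings form the pre/post pair.

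Two things remain. The analysis section does list its factors, and three that shape every mood series are not among them. Balance of order is promised over participants, and nothing says that it holds within condition or diagnostic group.

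**Conclusion.** The point holds as one of efficiency and interpretation. It does not affect the validity of the averaged condition contrast. For contrasts at given times, or pre/post contrasts that span the session, the loss is small for order effects up to 0.5 SD (power 0.81 to 0.78) and noticeable only near 1 SD (0.72, or 0.74 with exact balance in each arm). An uneven order split moves the estimate modestly: 0.50 becomes 0.48 or 0.45 at 60:40 or 70:30 in one arm. The documents report no such imbalance. The largest possible cost is dilution: an effect confined to one statement type would be halved in the pooled estimate, with power 0.31 to 0.37. All these sizes rest on assumed SDs, correlations, and order and carry-over effects, because the documents give none.

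**What to change.** In the HLM for depressed mood:

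1. Add phase (first/second), with time counted within phase from the preceding induction.
2. For contrasts among the active arms, also add stimulus type and order.
3. Keep the pooled CR + AFE versus CR contrast as the main one. Report condition-by-stimulus-type as a secondary analysis and a phase-1-only contrast as a sensitivity analysis.
4. For contrasts with sham, where no stimulus type is described, compare within phase.

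In the pre/post mood ANOVA, include order among the active arms wherever pre and post span the session.

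The cost is a few model terms based on information the sessions already generate. The secondary and phase-1-only estimates use fewer ratings and will be less precise.

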**Further psychophysiological measures**							
Facial muscle activity^c^	Biopac MP160				X		
Respiration rate (variability)	Biopac MP160				X		
Heart rate (variability)	Biopac MP160				X		
	24 GHz & 61 GHz CW Radar systems (self-developed)				X		
Verbal acoustics	Microphone		X		X		
**Technical app data (e.g.**,** reaction time**,** item choice**,** credibility of emotion display)**	EmpkinS EKSpression app				X		

Note. T0 = Screening; T1 = diagnostic session one week before the training; T2 = assessment directly before the training; T3 = assessment directly after training completion; T4 = assessment two weeks after training completion. SCID-5-CV = Structured Clinical Interview for DSM-5 Disorders Clinician version; GRID-HAMD = GRID Hamilton Rating Scale for Depression; PHQ-8/-9 = Patient Health Questionnaire-8/-9; CES-D = Centre for Epidemiological Studies Depression Scale; DAS-A = Dysfunctional Attitude Scale version A; ATQ-R = Automatic Thoughts Questionnaire-Revised; ERSQ-ES A = part A of the Self-Report Instrument for the Assessment of Emotion-Specific Regulation Skills; UEQ-S = User Experience Questionnaire, short version

^a^Measures are taken continuously during the training. ^b^The main purpose of the video recordings during T1 was to determine inter-rater reliability of the diagnostic interviews. ^c^We will use a bipolar electromyogram to measure activity of the musculus corrugator supercilii, musculus zygomaticus major, musculus masseter (only in the AFE condition), and musculus orbicularis oculi

The training session will take place one week after the diagnostic session at the laboratory, taking approximately three hours in total. At the beginning, participants will be randomly allocated to study conditions. We will use numbered, sealed envelopes containing the respective allocation information. The envelopes will be prepared by a student assistant not otherwise involved in the study. Following a pre-assessment (T2) on a computer tablet via Unipark.com and the setup of the kinesthetic and physiological data acquisition (see below for details), participants will receive brief psychoeducational instructions about the interconnection of cognitions (thoughts), the body (e.g., facial expression) and emotion/mood. Then, they will complete the 90-120-minute intervention on a study smartphone. The training session will be concluded with a brief self-report post-assessment (T3).

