**Fig. 3 Fig3:**
[figure not shown]
Trial flow of the four study conditions. CR = cognitive reappraisal training; CR + AFE = cognitive reappraisal training enhanced by instructions to deliberately display anti-depressive facial expressions; AFE = facial muscle training focusing on anti-depressive facial expressions

*CR*. To work with the cognitions, participants are instructed to respond to each of them in three steps. First, the screen will display three statements expressing *rejection* of the depressogenic cognition or *approval* of the anti-depressive cognition. Second, three statements *affirming* the rejection/approval, and third, three *self-supporting* statements will be presented on the screen. In each step, participants will choose the subjectively most fitting statement by selecting it on the screen and reading it aloud. To conclude the trial, participants again read aloud the affirming and self-supporting statement (depressogenic cognition training) or all three positive statements (anti-depressive cognition training) they have selected in a combined fashion.

*CR + AFE.* In the CR + AFE condition, participants will follow the same three steps as in the CR condition, except that they are instructed to mirror them with congruent kinesthesia including mime, posture, and gesture. Step 1 will be accompanied by rejection/approval, Step 2 by approval/confidence, and Step 3 by joy (trials 1 to 10) or pride (trials 11 to 20).

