In addition, the 21-item German version of the Automatic Thoughts Questionnaire-Revised (ATQ-R; [47]) will be administered. The ATQ assesses the frequency of positive and negative automatic thoughts (e.g., “My life is a mess”) during the previous week on a five-point Likert scale from 1 (*not at all*) to 5 (*all the time*). It has shown acceptable to good reliability in the general population (Cronbach’s alpha = 0.67-0.86) and good reliability in a patient sample (Cronbach’s alpha = 0.84-0.94; [47]).

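### Training statements are drawn from the Automatic Thoughts Questionnaire that is also scored as a secondary outcome, so an ATQ-R difference from sham may partly reflect practice on trained sentences

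*Protocol article*

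**What the plan says.** The section on training for the three intervention conditions names four scales as sources of the training statements, among them "the Automatic Thoughts Questionnaire (German version: [47"]). The items were "adapted and complemented by a team of three clinical psychologists with expertise in cognitive behavioral therapy for depression". How many come from each scale is not given.

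Under Secondary outcomes, "the 21-item German version of the Automatic Thoughts Questionnaire-Revised (ATQ-R; [47]) will be administered". On what it scores: "The ATQ assesses the frequency of positive and negative automatic thoughts", referring to the previous week. Table 1 marks the ATQ-R at T1, the diagnostic session one week before training, and at T4; the table note reads "T4 = assessment two weeks after training completion".

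The efficacy analysis section assigns mixed ANOVAs, with study condition at four levels including sham, to "secondary outcomes (i.e., GRID-HAMD, CES-D, current suicidality, ERSQ-ES, DAS-A, ATQ-R) assessed at pre-treatment, post-treatment, and/or follow-up".

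The arms differ in what they do with the statements. In CR, and in CR + AFE, which follows the same steps, "the screen will display three statements expressing *rejection* of the depressogenic cognition or *approval* of the anti-depressive cognition", and participants choose one and read it aloud. In AFE the statements are counteracted or strengthened with facial muscles. In the sham condition "the training consists of allocating geometric forms to a target object".

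**The concern.** The ATQ-R is there to show whether training changes automatic thinking. If some of its items, or close variants, were also training material, active participants meet sentences at T4 that they have spoken aloud and been coached to treat in a particular way. Sham participants have had no such coaching. A lower score in an active arm could then mean fewer automatic thoughts, or it could mean recognition of coached sentences and willingness to answer in line with the coaching. The total score does not separate the two.

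Blinding does not remove this. Participants are not told their condition, but the ATQ-R is self-report and they know which sentences they practised. The background section itself notes that patients can voice a functional statement without feeling or believing it, which is why a response on a drilled sentence is weak evidence of changed thinking.

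At stake is the interpretation of one secondary outcome, and of the cognitive mechanism it stands for, in the contrasts with sham.

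**Working it through.** The article gives no figure on this point to reproduce. The check is a cross-reading, followed by an illustration of size.

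**1. Is the source the same?** Both the training section and the outcome section cite reference 47. The first names the Automatic Thoughts Questionnaire, the second its revised 21-item German version, which the next sentence of the outcome section again calls the ATQ. Some overlap is therefore plausible. The item lists are not shown, so its extent is unknown.

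**2. Does exposure differ by arm?**

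| Arm | Contact with training statements |
|---|---|
| CR | Read aloud; depressogenic statements verbally rejected, anti-depressive ones verbally approved; 2 x 20 = 40 trials |
| CR + AFE | The same steps, with matching expression, posture and gesture |
| AFE | Read aloud; counteracted or strengthened by facial muscles, with no verbal rejection step |
| Sham | None in training |

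All arms read ten depressogenic cognitions aloud in the mood induction, and both mood induction phases are identical across arms. All arms also complete the ATQ-R at T1. Neither creates a difference between arms. The training phases do.

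**3. Is the overlap handled?** The efficacy analysis section neither drops nor separates shared items. The limitations paragraph in the Discussion says only that the statement sets are standardized and may not be equally relevant to everyone.

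**4. Possible size, first set of assumptions.** Let *k* of the 21 items be trained, let training shift each of these by 0.3 item-SD, let untrained items not move, and let Cronbach's alpha be 0.90. That alpha is an assumption, inside the 0.84 to 0.94 quoted for patients.

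- Mean inter-item correlation: 0.90 / (21 - 20 x 0.90) = 0.90 / 3 = 0.30.
- SD of the total, in item-SD units: sqrt(21 + 21 x 20 x 0.30) = sqrt(147) = 12.1.
- Shift in the total: *k* x 0.3 / 12.1 = 0.12 (*k* = 5), 0.25 (*k* = 10), 0.37 (*k* = 15).
- With *k* = 10, alpha 0.84 gives r = 0.84 / 4.2 = 0.20, SD = sqrt(105) = 10.2, shift 0.29. Alpha 0.94 gives r = 0.94 / 2.2 = 0.43, SD = 14.2, shift 0.21.

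**5. Possible size, second set of assumptions.** Assume 3 to 10 shared items, a shift of 0.25 to 0.5 scale points on each, and a change-score SD of 10 to 15. Pooling the diagnostic groups gives 256 / 4 = 64 per arm. Then *d* = items x shift / SD runs from 3 x 0.25 / 15 = 0.05 to 10 x 0.5 / 10 = 0.50. With no change in untrained thinking, a two-sample t-test at 0.05 would be significant in 6% to 80% of trials two-sided, or 9% to 88% one-sided. The one-sided figures are relevant because the plan allows one-tailed tests where the sign is specified.

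Both calculations say only that the distortion could be anything from negligible to material. None of the overlap counts, shifts or SDs comes from the article.

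**The case against.** Several points on the other side are sound.

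- **Overlap is inferred.** Items came from four scales and were adapted and supplemented. No sentence is shown to be in both lists. This stands, and it is why the first step of any remedy is to list the shared items.
- **Direction is not certain.** The ATQ-R asks how often thoughts occurred, not whether the respondent agrees with them. Reading depressogenic sentences aloud might make such thoughts more noticeable and raise reported frequency. This stands: a shift in favour of training is likely, not established.
- **Changing trained thoughts is partly the aim.** The background section describes functional thoughts becoming part of the patient's automatic thinking. A drop on trained items is therefore not pure artefact, and replacing the total score with untrained items would change the question to one of generalisation. This stands against replacing the total, but not against reporting the two parts alongside it.
- **The split will not be clean.** Untrained ATQ-R items may resemble trained items from the hopelessness, cognitive-triad or self-esteem scales. This is true and limits the precision of the remedy.
- **Two weeks pass after a single session.** That may weaken a practice effect; nothing shows that it removes it.

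A reader might also infer that all active arms are tested on sentences they rehearsed rejecting. The article does not support that: anti-depressive statements are approved rather than rejected, AFE has no verbal rejection step, and the number of shared items is unknown.

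**Conclusion.** The concern holds as a limit on interpretation. The ATQ-R contrasts with sham mix any effect of practice on trained sentences with change in automatic thinking, and the planned total score cannot separate them. This rests on the shared source, the different exposure by arm and the four-condition comparison, all stated in the article, and on the assumption that at least some of the 21 scored items survive in recognisable form in the training set.

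The size is undetermined. The illustrative 0.12 to 0.37 SD, and the wider *d* of 0.05 to 0.50, depend wholly on assumed overlap, shift and variance. A reader might infer from the upper end of the first range that practice alone could supply about three quarters of the *d* = 0.5 used for planning (0.37 / 0.5 = 0.74). That would need 15 of the 21 items to be trained and the assumed shift to persist for two weeks, and the article does not tie *d* = 0.5 to the ATQ-R.

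The reach is narrow. The primary outcome, momentary depressed mood, is not affected. CR + AFE versus CR, the augmentation question, is largely spared because both arms work through the same steps on the statements. This is a cheap improvement to one secondary outcome, not a flaw in the trial's main comparison.

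**What to change.** Before unblinded analysis:

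1. List the ATQ-R items that appear in the stimulus set, including in adapted form, with the rule used to classify adapted items.
2. Keep the ATQ-R total and its mixed ANOVA as planned.
3. Prespecify two further scores for the contrasts with sham, one for trained and one for untrained items.
4. Claim a general change in automatic thoughts relative to sham only if the untrained-item score supports it. Use the DAS-18-A as companion evidence: it is already collected at T1 and T4 and is not a listed stimulus source.
5. Name the overlap among the limitations.

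The cost is rescoring, with no new data. The untrained subscale is shorter and less reliable. With the assumed inter-item correlation of 0.30 and *m* items left, alpha = 0.30*m* / (1 + 0.30(*m* - 1)): 4.8 / 5.5 = 0.87 for 16 items, 3.3 / 4.0 = 0.83 for 11, and 1.8 / 2.5 = 0.72 for 6, against 0.90 for all 21. Classifying adapted items needs some judgement, best exercised without sight of outcome data by arm.
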